### 7.6.3 FOLLOW-UP PROCEDURES AND VISITS

#### **Days 0-6**

The study staff will contact the participant/parent(s)/LAR by telephone three days after vaccination (Day 3 Phone call) to ensure the completeness of Diary Card and to check the health status of their participants and remind the date of the next visit day.

#### **Visit 3 – Safety follow-up visit (Day 7 $\pm$ 2 day)**

- 1) Record solicited and unsolicited adverse events since the last visit in eCRF
- 2) Verify that the participant/parent(s)/LAR fill in the diary card 1 correctly
- 3) Perform clinical examination (including vital signs and general physical exam) and record in eCRF
- 4) Collect interval medical history in order to capture any AEs and SAEs through interview
- 5) Hand over the diary card 2 to be filled till day 28 post vaccination
- 6) Schedule next visit, i.e. V4 and remind the participant parent(s) or legal guardian to contact investigator/ study staff if needed

#### **Visit 4 – Follow-up visit (Week 4, Day 28 $\pm$ 3 days)**

- 1) Check diary card 2 and confirm with participant/parent(s)/LAR before recording observations in the eCRF
- 2) Perform clinical examination including vital signs, general physical examination
- 3) Collect interval medical history in order to capture any AEs and SAEs through interview. Record any unsolicited AE, SAE, and concomitant medications in eCRF
- 4) Perform blood draw (from Adult stratum) for assessment of immune responses post vaccination
- 5) Schedule next visit i.e. V5 and hand over diary card 3 to participant/parent(s)/LAR to capture any SAEs till 24 weeks (168 days) post vaccination

### **Visit 5 - Follow-up visit (Week 24, Day 168 ± 7 days)**

This is the final visit of the study.

- 1) Collect diary card 3 and check with participant/parent(s)/LAR before recording observations in the eCRF
- 2) Perform clinical examination including vital signs, general physical examination
- 3) Collect interval medical history in order to capture any SAEs through interview. Record any SAE and concomitant medications in eCRF
- 4) Ensure source documents are duly completed before the participant/parent(s)/LAR leave the study center
- 5) Participant will be continued to be monitored after study ends for unresolved AE

While in the study the female participant of child bearing age should not get pregnant. As such they should discuss with their study doctor if their current contraception can give them a reliable protection against getting pregnant. If any participant becomes pregnant during the conduct of the study, then the participant would be followed up until delivery and informations will be captured in pregnancy form. Detailed information regarding pregnancy such as method of delivery, duration of pregnancy and outcome to both mother and baby will be captured and mentioned in safety management plan.

## **7.7 PARTICIPANT WITHDRAWAL OR TERMINATION**

### **7.7.1 REASONS FOR WITHDRAWAL OR TERMINATION**

Participant/parent(s)/LAR are free to withdraw from participation in the study at any time upon their request, without justification and without any effect to the standard healthcare due to them.

The Site Investigator may also decide to discontinue participation of a participant from study interventions in the following cases:

- 1) An acute reaction (allergy, hypersensitivity reaction, etc.) to the investigational product
- 2) Occurrence of an illness or serious adverse event or adverse event that in the judgment of the investigator may be detrimental for the participant's safety
- 3) A study participant/parent(s)/LAR withdrawal of informed consent
- 4) A study participant's medical condition or use of medication that in the judgment of the investigator may compromise the participant's safety and/or the scientific integrity of the study
- 5) Violation of the inclusion/exclusion criteria by the participant
- 6) A study participant's no-show for a scheduled visit without notice, unable to contact/trace, and lost to follow-up
- 7) Any other reason of study discontinuation as per the judgment of the site Investigator

---

#### 7.7.2 HANDLING OF PARTICIPANT DISCONTINUATION OR TERMINATION

Discontinuation from study intervention does not mean discontinuation from the study, and remaining study procedures will be completed as indicated in the study protocol. If a clinically significant finding is identified after enrollment, the PI will determine if any change in participant management is needed. Any new clinically relevant finding will be reported as an adverse event.

Study team will encourage withdrawn or terminated participant to continue in the study for safety follow-up. If participant/parent(s)/LAR decline, this will end the participant's/parent(s)/LAR's interaction with the study team for this protocol. The study team will engage in no further communication with the volunteer except as directed by an IRB with regard to participant safety information. Protocol-specified safety follow-up procedures will be discussed with the participant/parent(s)/LAR to capture AEs, SAEs. The reason for participant discontinuation or withdrawal from the study will be recorded on the study follow-up eCRF. Only data and samples already collected will be analyzed according to protocol. Counseling about any issue will be provided if participant/parent(s)/LAR decide to discontinue participation in the study. Medical advice will also be provided in the best interest of the participant.

Participants who receive the study intervention and subsequently withdraw, or are withdrawn or discontinued from the study will not be replaced.

In the event of early termination of a participant:

- 1) Date and Reason for early termination of the participant will be recorded in the eCRF
- 2) Any unsolicited AE, SAE and concomitant medications up to that points will be recorded in eCRF
- 3) Clinical examination including vital signs, and general physical examination will be performed if participant/parent(s)/LAR is/are willing

## 7.8 LOST TO FOLLOW-UP

A participant will be considered lost to follow-up if he or she fails to return for any of scheduled visits and remains unreachable to study site staff.

The following actions will be taken if a participant fails to return to the site for a required study visit:

- The site staff will attempt to contact the participant/parent(s)/LAR and counsel on the importance of maintaining the assigned visit schedule and ascertain if the participant/parent(s)/LAR wishes to and/or should continue in the study
- Before a participant is deemed lost to follow-up, the investigator or designee will make every effort to regain contact with the participant/parent(s)/LAR (will make at least 3 telephone calls on separate days). These contact attempts should be documented in the participant's medical record or study file

Should the participant continue to be unreachable, he/she will be considered to have withdrawn from the study with a primary reason of lost to follow-up.

## 7.9 PROTOCOL DEVIATIONS

A protocol deviation is any non-compliance with the clinical trial protocol or GCP by the participant, the investigator, or the study site staff. It is the responsibility of the site investigator to use continuous vigilance to identify and report all major protocol deviations to site IRB and sponsor. Minor protocol deviations could be reported to IRBs along with periodic study report submission as per local IRBs requirements. The site investigator is responsible for knowing and

adhering to the site IRB requirements. The IVI Study Medical Monitor will report all protocol deviations to IVI IRB.

Major deviations are defined as those jeopardize the safety or rights of the participant or the scientific integrity of the study which may be applicable to cases listed below.

- Violation of inclusion and exclusion criteria
- Vaccination with wrong vaccine as defined in the protocol
- Visit outside window for the immunogenicity assessment after discussion with the study medical monitor
- Missed samples for immunogenicity

Major protocol deviations thought to affect the scientific integrity of the study will be reported and discussed with investigator, monitor, sponsor, and statistician for their exclusion from the per protocol analysis. For minor protocol deviations considered not to affect the scientific integrity of the study, the extent of deviation or delay as well as reason will be accurately documented.

#### 7.10 PROTOCOL AMENDMENTS

Any amendment of the approved protocol shall be submitted to all IRBs (IVI and site IRBs) and to the National Regulatory Authority (PFDA) for information and approval before implementation.

#### 7.11 PREMATURE TERMINATION OR SUSPENSION OF STUDY

This study may be temporarily suspended or prematurely terminated if there is sufficient reasonable cause as per PI recommendation after consultation with sponsor. PFDA, site IRBs independent Data Safety Monitoring Board (i.e., DSMB) and Safety Monitoring Committee (i.e., SMC) may also instruct for suspension or termination of the study. Written notification, documenting the reason for study suspension or termination, will be provided by the suspending or terminating party to investigator, the sponsor, the regulatory authorities, and IRBs.

Circumstances that may warrant termination or suspension are:

- Determination of unexpected, significant, or unacceptable risk to participant as recommended by the PI

- Poor protocol compliance

Study may resume once concerns about safety, protocol compliance, data quality are addressed and satisfy the sponsor, PFDA, Site IRBs or DSMB/SMC.

#### 7.12 END OF STUDY

A participant is considered to have completed the study if he or she has completed all procedures of the study including the last visit or the last scheduled procedure shown in the Schedule of Events (SOE).

### 8 LABORATORY PROCEDURES/EVALUATIONS

#### 8.1 SPECIMEN PROCESSING, HANDLING, AND STORAGE

Venous blood will be collected from participants for immunogenicity assessments from adult stratum only. Whole blood will be centrifuged, and sera will be aliquoted and stored at below -20°C until shipment to IVI and storage for future use. Pre-print study labels provided in advance will be attached on each of the serum aliquots.

#### 8.2 SPECIMEN SHIPMENT

Aliquoted blood samples for immunogenicity assessment will be shipped from clinical trial site to the International Vaccine Institute, Seoul, Republic of Korea, where they will be stored at -70°C for analysis and storage for 10 years after completion of CSR or according to subject's decision about preservation period.

#### 8.3 ASSESSMENT OF IMMUNOGENICITY

##### *Anti-Vi IgG ELISA*

The assay is used to measure anti-Vi specific antibodies of the IgG in human sera. Poly-L-lysine is pre-coated and purified Vi antigen at a concentration of 2 µg/mL is absorbed onto 96-well

microtiter plates. Non-specific binding sites are blocked with Bovine Serum Albumin (BSA) in Phosphate Buffered Saline (PBS), diluted human sera is then added to the first wells in the plate then serially diluted across the plate. Antibodies specific to Vi will bind to the Vi coated to the plate. The bound IgG is detected using alkaline phosphatase labelled goat anti-human IgG. Addition of 4-nitrophenyl phosphate substrate causes a color change proportional to the amount of human anti-Vi IgG antibody present in the serum. Optical Densities of the wells are measured at 405 nm. The level of the specific anti-Vi IgG in ELISA units for each serum sample is determined by comparison to a reference serum.

## 9 ASSESSMENT OF SAFETY

### 9.1 SAFETY ASSESSMENT

The following procedures will be performed to monitor safety as listed in the SOE:

- **Demographic and medical history** (*DOB, age, gender, baseline medical history of participants*)
- **Physical examination** (*height/length and weight, organ systems, growth and development and motor assessments for age eligible participants*)
- **Vital signs** [*temperature, pulse, respirations, blood pressure (only for 18-45 years)*]
- **Diary cards** will be used for participant/parent(s)/LAR reported outcomes

At each study visit, the investigator will inquire about the occurrence of AE/SAEs since the last visit.

#### 9.1.1 DEFINITION OF ADVERSE EVENTS (AE)

**Adverse events (AE):** These are defined as any untoward medical occurrence which follows immunization and which does not necessarily have a causal relationship with the administration of the vaccine. An AE may be any unfavorable or unintended sign, symptom, abnormal laboratory finding or disease.

**Adverse Drug Reactions (ADR):** All noxious and unintended responses to a medicinal product related to any dose should be considered adverse reactions (AR). The phrase “responses to a medicinal product” means that a causal relationship between a medicinal product and an AE is exist with at least a reasonable possibility.

**Solicited AEs** are predetermined events, identified in the Investigator's Brochure (IB), which may reflect safety concerns related to the investigational product. AEs that will be solicited by the participant/ parents/LAR and recorded in the diary card and reviewed by a blinded observer during the 7 days after each dose for this study include:

- Local reactions at the site of injection: pain/tenderness, erythema/redness, induration/swelling, pruritus associated with injection
- Systemic reactions (adapted by age group): fever, lethargy, irritability, nausea/vomiting, arthralgia, diarrhea, drowsiness, loss of appetite, chills, headache, fatigue, myalgia and persistent crying

Among the various systemic reactions headache, fatigue, myalgia will be captured only for 2 to 45 years subjects while persistent crying will be captured only for 6 months to 2 years subjects. The rest of the systemic reactions will be captured in all age strata. This is also clearly mentioned in the diary cards.

**Unsolicited AEs** are all other adverse events (those that do not fall under the categories of solicited Adverse Reactions) that are identified by site staff, the site investigator and the Safety Medical Monitors. These unsolicited AEs will be documented in the participant's study records and entered in the study eCRFs.

Results will be expressed as frequency of the AEs and individual descriptions will be tabulated according to MedDRA organ class system.

---

#### 9.1.2 DEFINITION OF SERIOUS ADVERSE EVENTS (SAE)

An AE or suspected adverse reaction is considered "serious" if, in the view of either the investigator or sponsor, it results in any of the following outcomes:

- Results in death
- Life-threatening event
- Requires in-patient hospitalization > 24 hours or prolongation of existing hospitalization
- Results in persistent or significant incapacity or substantial disruption of the ability to conduct normal life functions
- Congenital anomaly/birth defect
- Important medical events that may not result in death, be life-threatening, or require hospitalization may be considered serious when, based upon appropriate medical judgment, they may jeopardize the participant and may require medical or surgical intervention to prevent one of the outcomes listed in this definition.

### 9.1.3 DEFINITION OF SUSPECTED UNEXPECTED SERIOUS ADVERSE EVENT (SUSAR)

**Suspected unexpected serious adverse event (SUSAR)** is defined as a serious adverse reaction whose nature or severity is not consistent with the applicable product information, VI-DT Investigator's Brochure or the summary of product characteristics of an authorized product.

## 9.2 CLASSIFICATION OF AN ADVERSE EVENT

### 9.2.1 SEVERITY OF EVENT

All solicited AEs in the study will be graded for their severity and recorded in the eCRF as described in below table. All other AEs will be assessed by the study clinician using the National Institute of Allergy and Infectious Diseases (NIAID) Division of AIDS Table for grading the severity of Adult and Pediatric Adverse events [28].

**Table 5. Solicited systemic adverse reaction severity grading**

| Systemic (General) | Mild (Grade1)                  | Moderate (Grade2)                         | Severe (Grade3)                            | Potentially Life Threatening (Grade 4) |
|---------------------------|---------------------------------------|--------------------------------------------------|---------------------------------------------------|-----------------------------------------------|
| Fever*                    | 38.0 – 38.5°C                         | 38.6 – 39.2°C                                    | 39.3 – 39.9°C                                     | ≥ 40°C                                        |
| Lethargy                  | No interference with routine activity | Some interference with routine activity          | Significant; prevents daily routine activity      | ER visit or hospitalization                   |
| Irritability              | Require minimal or no treatment       | Results in low level of inconvenience or concern | Interrupt daily activity and require drug therapy | ER visit or hospitalization                   |
| Nausea/
Vomiting       | No interference with routine activity | Some interference with routine activity          | Significant; prevents routine daily activity      | ER visit or hospitalization                   |

|                   |                                                             |                                                               |                                                          |                                                   |
|-------------------|-------------------------------------------------------------|---------------------------------------------------------------|----------------------------------------------------------|---------------------------------------------------|
| Arthralgia        | No interference with routine activity                       | Some interference with routine activity                       | Significant; prevents daily routine activity             | ER visit or hospitalization                       |
| Diarrhea          | No Interference with routine activity 1-2 episodes/24 hours | Some Interference with routine activity > 2 episodes/24 hours | Prevents daily activity requires outpatient IV hydration | ER visit or hospitalization for hypotensive shock |
| Drowsiness        | No interference with routine activity                       | Some interference with routine activity                       | Significant; prevents daily routine activity             | ER visit or hospitalization                       |
| Loss of appetite  | Require minimal or no treatment                             | Results in low level of inconvenience or concern              | Require drug therapy                                     | ER visit or hospitalization                       |
| Chills            | No interference with routine activity                       | Some interference with routine activity                       | Significant; prevents daily routine activity             | ER visit or hospitalization                       |
| Headache          | No interference with routine activity                       | Some interference with routine activity                       | Significant; prevents daily routine activity             | ER visit or hospitalization                       |
| Fatigue           | No interference with routine activity                       | Some interference with routine activity                       | Significant; prevents daily routine activity             | ER visit or hospitalization                       |
| Myalgia           | No interference with routine activity                       | Some interference with routine activity                       | Significant; prevents daily routine activity             | ER visit or hospitalization                       |
| Persistent crying | Require minimal or no treatment                             | Results in low level of inconvenience or concern              | Interrupt daily activity and require drug therapy        | ER visit or hospitalization                       |

\* Axillary temperature will be recorded.

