#### Secondary Endpoints

- Seroconversion rates (defined as a 4-fold increase of serum anti-Vi IgG antibody titer from baseline) of anti-Vi IgG ELISA antibody titers at 4 weeks (28 days) after vaccination with Vi-DT(MD) / Vi-DT (SD) compared to baseline (D0) [18-45 year age stratum]
- Comparison of safety of V-DT compared to control: Vi-DT MD and SD will be compared separately to control vaccine and will be compared by age strata at 4 weeks after vaccination
  - Local and systemic solicited adverse events during the 7 days after vaccination  
(Refer to Table 5 and 6 for details of grading of AEs)

- Solicited local reactions at the site of injection: pain, tenderness, erythema/redness, swelling/ induration, pruritus
- Solicited Systemic reactions (adapted to each age group): fever, lethargy, irritability, nausea/vomiting, arthralgia, diarrhea, drowsiness, loss of appetite, chills, headache, fatigue, myalgia and persistent crying
- Unsolicited adverse events during 4 weeks (28 days) after vaccination
- Serious Adverse Events during the entire study period

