**Table 6. Solicited local adverse reaction severity grading**

| Local Reaction to Injectable Product | Mild (Grade 1) | Moderate (Grade 2) | Severe (Grade 3) | Potentially Life Threatening |
|---------------------------------------------|-----------------------|---------------------------|-------------------------|-------------------------------------|
|---------------------------------------------|-----------------------|---------------------------|-------------------------|-------------------------------------|

|                                                           |                                          |                                                                                |                                                                           | (Grade 4)                             |
|-----------------------------------------------------------|------------------------------------------|--------------------------------------------------------------------------------|---------------------------------------------------------------------------|----------------------------------------------|
| Pain /Tenderness                                          | Does not interfere with routine activity | Interferes with routine activity or repeated use of non-narcotic pain reliever | Prevents routine daily activity or repeated use of narcotic pain reliever | Emergency room (ER) visit or hospitalization |
| Erythema/Redness
(Adolescents & adults, age ≥12yrs)    | Affected area 25 - < 50mm in diameter    | Affected area 50-<100mm in diameter                                            | Affected area ≥ 100 mm in diameter                                        | Necrosis or exfoliative dermatitis           |
| Erythema/Redness
(Children, age 2<12 yrs)              | < 25 mm in diameter                      | 25 – 50 mm in diameter                                                         | ≥ 50 mm in diameter                                                       | Necrosis or exfoliative dermatitis           |
| Erythema/Redness
(Children, age < 2 yrs)               | < 10 mm in diameter                      | 10 < 25 mm in diameter                                                         | 25 < 50 mm in diameter                                                    | ≥ 50 mm in diameter                          |

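### Table 5 grades irritability, persistent crying and loss of appetite on mixed, overlapping criteria, so their recorded severity can be wrong by an amount the protocol does not let us compute

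*Protocol*

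**What the plan says.** Section 9.2.1 makes the tables binding: "All solicited AEs in the study will be graded for their severity and recorded in the eCRF as described in below table". Section 5.1 ties the solicited-reaction part of the secondary safety endpoint to the same tables: "Refer to Table 5 and 6 for details of grading of AEs".

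Table 5 lists 13 systemic reactions. For irritability and persistent crying the cells read:

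- Grade 1: "Require minimal or no treatment"
- Grade 2: "Results in low level of inconvenience or concern"
- Grade 3: "Interrupt daily activity and require drug therapy"

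Loss of appetite has the same Grades 1 and 2, but its Grade 3 is only "Require drug therapy". In all three rows Grade 4 is an emergency-room visit or admission.

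Eight other rows (lethargy, nausea/vomiting, arthralgia, drowsiness, chills, headache, fatigue, myalgia) use interference with activity for Grades 1 to 3. Their Grade 3 is "Significant; prevents daily routine activity", with a trivially different word order for nausea/vomiting.

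**The concern.** A severity scale needs grades that are ordered and do not overlap. In these three rows the criterion changes from treatment (Grade 1) to impact (Grade 2), and then to both or to treatment alone (Grade 3). The recorded grade can then follow the view taken on drug therapy rather than how severe the reaction was, and two investigators who both follow the table can grade the same event differently.

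At stake is the severity profile of these terms. Section 4 makes describing safety in each age stratum a secondary objective. Under Section 9.1.1, persistent crying is collected only in the youngest stratum, and irritability and loss of appetite in all strata. Section 3.4.1 states that reactions are expected to be mild or moderate, so a scale that can place an activity-stopping reaction in the mild column leans towards the stated expectation. The grade is assigned at data capture, so an analysis plan can repair it later only as far as source records describe the impact.

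**Working it through.** No formula applies, and the protocol gives no figure to reproduce. The check is a cell-by-cell reading of Table 5.

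**Rows affected.** The 13 systemic rows divide as follows: 8 on interference alone, 3 with the mixed wording, 1 on temperature (fever) and 1 that combines interference with episode counts and hydration (diarrhea); 8 + 3 + 1 + 1 = 13. By age, Section 9.1.1 omits headache, fatigue and myalgia in the youngest stratum, leaving 13 − 3 = 10 systemic terms, of which 3 are affected. From age 2 it omits persistent crying, leaving 13 − 1 = 12, of which 2 are affected.

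**Literal application.** None of these test cases involves an emergency visit or admission, so Grade 4 is out.

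| Case | Grade 1 | Grade 2 | Grade 3 | Literal result |
|---|---|---|---|---|
| Irritability or crying; daily activity stopped; drug judged not required | Met (no treatment required) | Not met (the impact is not low) | Not met (only half of the joint condition holds) | Grade 1 only |
| Any of the three; low concern; no treatment required | Met | Met | Not met | Grades 1 and 2 |
| Loss of appetite; little impact; drug required | Does not govern if drug therapy is required | Impact wording met | Met (drug therapy is enough) | Grade 3 despite low impact |
| Loss of appetite; daily activity stopped; drug judged not required | Met | Not met | Not met | Grade 1 only |

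**Comparison with the other rows.** The impact in the first and fourth cases is Grade 3 in each of the eight interference rows, where preventing daily activity is sufficient. Table 6 shows a third construction: for pain/tenderness, Grade 3 is "Prevents routine daily activity or repeated use of narcotic pain reliever", so impact and treatment are alternatives. Across the two tables, impact alone reaches Grade 3 in some rows, impact or treatment in one, impact and treatment together in two, and treatment alone in one.

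**Is there a tie-break elsewhere?** Section 9.3 asks for changes in severity over time to be documented. That covers an event whose severity changes, not one that meets the wording of two grades at once. No section says which grade to record when two fit.

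**Direction and size.** For irritability and crying, the joint condition at Grade 3 can only withhold that grade from an activity-stopping episode, so the literal risk is under-grading. For appetite, the third and fourth cases point in opposite directions and the net effect is unknown. The protocol gives neither the frequency of such episodes nor how often they would be judged to require a drug, so no size follows.

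**The case against.** The strongest reply is that grading is clinical, not mechanical. The cells speak of a reaction that requires drug therapy, not one that received it. An investigator who judges that an inconsolable infant needed treatment can assign Grade 3 even if nothing was given. Sections 9.3 and 9.4.1 leave severity to the clinician, and the columns are headed mild, moderate and severe. This stands in part: Grade 1 is the literal result for an activity-stopping episode judged not to require a drug, but not a certain one. It does not cure the overlap of Grades 1 and 2 or give investigators a common rule.

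The consequence is also limited, and this stands. Section 5.1 names no severe-reaction rate as an endpoint. Section 11.5.3 summarises events and proportions of participants descriptively, and whether a reaction occurred does not depend on its grade. Serious events are classified by outcome under Section 9.1.2. One scale serves all three groups, graded by blinded staff, so nothing suggests differential grading between arms. That does not protect the absolute proportions by grade within a group.

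Diarrhea also combines activity with a treatment criterion at Grade 3. The sponsor may wish to read that row at the same time, but it keeps activity in Grades 1 to 3 and does not share the wording at issue.

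A reader might go further and infer that severe reactions will be reported as mild, or attach a percentage to the shortfall. The documents support neither. Judgement can move the grade, the appetite row can over-grade, and any percentage would only restate an assumed share of episodes not requiring a drug.

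**Conclusion.** The point holds as a defect in three rows of a binding grading table. The grades for irritability, persistent crying and loss of appetite are neither mutually exclusive nor ordered on one axis. Irritability and crying can be under-graded; appetite can be mis-graded in either direction. This rests on reading the cells as written, given that the protocol supplies no tie-break.

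Its reach is 3 of 13 solicited systemic terms (3 of 10 in the youngest stratum, 2 of 12 from age 2), and only their severity grades. The amount of misgrading cannot be computed. The GMT and seroconversion equivalence analyses, the sample size, adverse event counts and serious adverse events are untouched. It is worth correcting because the change is cheap and the severity description by stratum serves a stated objective, not because any conclusion of the trial is known to be biased.

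**What to change.** Reconcile the three rows to one stated, non-overlapping basis. The documents do not show which basis was intended, so the sponsor must decide; the simplest choice is the interference-with-activity wording already used in eight rows of Table 5, with Grade 4 left as it is. Keep drug treatment as a separate item; it is already collected as concomitant medication and in the event record under Section 9.3. Once the rows are reconciled, state that the highest applicable grade is recorded. Adding that rule to the present wording would only move untreated events of low concern into Grade 2. Align the diary and eCRF text.

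Enrolment had begun before the March 2020 lockdown described under the age strata reassignment, so events may already be graded on the present wording. Regrade those blinded and before database lock where source records describe the impact, and flag those that cannot be regraded so that two scales are not mixed unnoticed.

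The cost is a wording amendment, a small regrading effort and possibly a few more events graded severe. Participant care does not change.
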